## Abstract

**Background:**

Rotator cuff tendinopathy and subacromial impingement syndrome present complex patomechanical situations, frequent difficulties in clinical diagnosis and lack of effectiveness in treatment. Based on clinical experience, we have therefore considered the existence of another pathological entity as the possible origin of pain and dysfunction. The hypothesis of this study is to relate subacromial impingement syndrome (SIS) with myofascial pain syndrome (MPS), since myofascial trigger points (MTrPs) cause pain, functional limitation, lack of coordination and alterations in quality of movement, even prior to a tendinopathy. MTrPs can coexist with any degenerative subacromial condition. If they are not taken into consideration, they could perpetuate and aggravate the problem, hindering diagnosis and making the applied treatments ineffective.

The aims and methods of this study are related with providing evidence of the relationship that may exist between this condition and MPS in the diagnosis and treatment of rotator cuff tendonitis and/or SIS.

**Method/design:**

A descriptive transversal study will be made to find the correlation between the diagnosis of SIS and rotator cuff tendonitis, positive provocation test responses, the existence of active MTrPs and the results obtained with ultrasonography (US) and Magnetic Renonance Imaging (MRI). A randomized double blinded clinical trial will be carried out in experimental conditions: A Protocolized treatment based on active and passive joint repositioning, stabilization exercises, stretching of the periarticular shoulder muscles and postural reeducation. B. The previously described protocolized treatment, with the addition of dry needling applied to active MTrPs with the purpose of isolating the efficacy of dry needling in treatment.

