### In Relation to Treatment

#### Design: Random clinical trial

The subjects included in the study will be randomized (with a hidden sequence) to two sets of experimental conditions:

1. – Protocolized treatment based on active and passive joint repositioning, stabilization exercises, stretching of the periarticular shoulder muscles and postural reeducation.

2. – The previously described protocolized treatment with the addition of dry needling of active MTrPs on the supraspinatus, infraspinatus, subscapularis and teres minor muscles using Hong's fast-in and fast-out technique, once for each active MTrP and accompanied by a cold spray to reduce the painful post-needling sensation. Only one needling will be performed in each session with an interval of 8 days between sessions.

The purpose of these treatment methods is to isolate the efficacy of dry needling in the treatment of rotator cuff tendonitis and/or SIS.

Training and standardization sessions will be held for both protocols so that the intervention will be the same for all subjects in the study.

The treatment will consist of 10 physiotherapy sessions and the measuring of dependent variables will be made during the initial visit and at the end of the treatment. The final and follow-up measuring will be performed by a blind evaluator.

The sample size is 132 patients (with and error of 0.05 and a power of 80%, if a correlation of 0.25 of the sample size is taken to be 120 patients; expecting a 10% attrition, the necessary sample size would be 132 patients). The patients will be randomized to include 66 subjects in each therapy method.

The study variables related to treatment are shown on the table 2:

**Table 2 T2:** Study Variables Related to Treatment

INDEPENDENT VARIABLE	DEPENDENT VARIABLE	
THERAPY METHOD	Joint restriction by	Flexion-extension movements
		
	digital inclinometer	Abduction-adduction movements
		
		Lateral-medial rotation movements
	
A. Protocolized treatment	Pain on elevation in the scapular plane	VAS scoring
		
		Location of pain
	
B Protocolized treatment + dry needling of MTrPs	Function Constant Test	
	
	Existence of active MTrPs by algometry	Supraspinatus
		
		Infraspinatus
		
		Subescapularis
		
		Teres minor

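### The abstract calls the trial double-blind, but the design described blinds only the evaluator, and the contrast estimates an add-on effect of needling with cold spray rather than needling in isolation

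*Protocol article*

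**What the plan says.** The abstract of the protocol article, under Method/design, states: "A randomized double blinded clinical trial will be carried out in experimental conditions". The section In Relation to Treatment carries the plainer heading "Design: Random clinical trial". It says that the allocation sequence is hidden and, on blinding, only that "The final and follow-up measuring will be performed by a blind evaluator".

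That section defines the two arms as follows:

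- First arm: "Protocolized treatment based on active and passive joint repositioning, stabilization exercises, stretching of the periarticular shoulder muscles and postural reeducation".
- Second arm: "The previously described protocolized treatment with the addition of dry needling of active MTrPs" in four rotator cuff muscles, each active trigger point being needled once, "accompanied by a cold spray to reduce the painful post-needling sensation".

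On what the comparison is for, the same section says: "The purpose of these treatment methods is to isolate the efficacy of dry needling". The abstract states the same purpose. Table 2 lists the dependent variables: joint restriction by inclinometer, pain on elevation (VAS score and location), the Constant test, and active trigger points by algometry.

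**The concern.** A double-blind label tells the reader that expectation on the patient's side has been controlled. In the arms described, one group has needles inserted into painful muscle and the other has nothing in their place, so that control cannot exist for the patient. The body of the article does not claim it either.

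The stated purpose has a related problem. The arms differ by the needling, by the cold spray that goes with it, and by the experience of an additional procedure. Their difference is the effect of that package on top of physiotherapy.

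What is at stake is how a positive result would be described. Pain is rated by people who know whether they were needled. If a pain difference were reported under the abstract's label and stated purpose, readers would take it as double-blind evidence of the specific efficacy of needling, which this design cannot supply.

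**Working it through.** No arithmetic bears on this point. The sample-size figures (120, then 132) do not enter it. The check is a comparison of what the article says in different places.

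**Step 1: who is blinded.**

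| Role | What the article says |
|---|---|
| Outcome evaluator | Blind at final and follow-up measurement (In Relation to Treatment) |
| Patient | No masking described |
| Person who needles | No masking described; not identified |
| Person delivering the common physiotherapy | No masking described; not identified |
| Analyst | No masking described (Data analysis) |

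One role is stated to be blind. The hidden sequence is allocation concealment: it protects the assignment up to the moment it is made and does not supply a second blinded party.

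**Step 2: whether patients could be blind even though the article does not say so.** The second arm is defined as the first arm's programme with needling added, and the first arm's list contains no sham procedure. Needling is a procedure the patient can feel, and the article itself expects it to leave a painful sensation. A patient in the second arm knows that needles were used, and a patient in the first arm knows that they were not. No sentence says that patients are unblinded. It follows from the definitions of the arms, and the same reasoning covers whoever inserts the needles.

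**Step 3: what the contrast contains.**

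| Component | First arm | Second arm |
|---|---|---|
| Protocolized physiotherapy | yes | yes |
| Dry needling | no | yes |
| Cold spray | not listed | yes |
| Additional procedure and the expectation attached to it | no | yes |

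The common programme cancels between arms and the other three rows do not. The estimate is therefore the effect of adding needling with cold spray, under open conditions for the patient.

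**Step 4: which outcomes are exposed.** The patient is the source of the VAS score and of the location of pain. A blind evaluator can record both without influencing them, but cannot remove the patient's knowledge of the treatment. The article does not describe how far the other outcomes in Table 2 depend on the patient's report, so this point is confined to those two.

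**The case against.** **The unsupported term occurs once, in an abstract, and the body is accurate.** This is true, and it makes the correction easy. But the abstract positively asserts a design property that the described arms cannot have, so this is not a detail merely left out by a condensed article. A full protocol might also name a blinded analyst, and some would count that as the second party. Even then, the label would lead most readers to think that patients were blinded, and naming the blinded roles removes the ambiguity.

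**An add-on comparison is legitimate and needs no sham.** This stands. The aim regarding treatment compares needling with usual clinical protocols, which is an add-on question. The cold spray is openly described as an adjunct of the needling. Isolating can be read as separating needling from the shared programme. That reading is fair, but the wording also invites the stronger one of specific efficacy, and restating the purpose settles which is meant.

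**Readings that go too far.** A reader might infer the following, and the article does not support them:

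- *Every treating physiotherapist knows the allocation.* The article does not say who needles, or whether the same person delivers the common programme. Only the person needling certainly knows.
- *Part of the Constant test is patient-reported and so exposed as well.* The article names the test but does not describe its components.
- *The bias can be expressed as a share of the effect the trial is sized for.* The article gives only a correlation of 0.25, tied to no outcome. It can be converted, d = 2r/√(1 − r²) = 0.50/√0.9375 = 0.516, but nothing says that it was meant as a difference between arms in pain. Any size for an expectation effect would also be the reader's own assumption.
- *Efficacy should rest first on the inclinometer measurements.* That would impose an order on the outcomes which the article does not set, so it is more than a wording change. It would not fully solve the problem either, since movement of a painful shoulder can depend on the effort of a patient who knows the treatment.

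**Conclusion.** The concern holds in a limited form. The double-blind label is wrong as written: the article supports evaluator blinding at final and follow-up measurement and no more, and patients cannot be blind to needling in the arms described. The stated purpose claims more than the comparison can deliver, which is the effect of adding needling with cold spray to protocolized treatment.

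The consequence is clearest for VAS pain and pain location, where a positive result should not be presented as double-blind, isolated efficacy. Its size cannot be stated from the documents, which contain nothing from which a bias could be estimated.

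The conclusion rests on one inference: that the first arm receives nothing resembling needling. Both the abstract and the design section define that arm without any such element. The absence of a sham is a design choice and is not itself criticised here.

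**What to change.** Three changes of description:

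1. In the abstract, replace the double-blind label with *evaluator-blinded (patients not blinded)*.
2. In the abstract and in the section In Relation to Treatment, restate the purpose as estimating the effect of adding dry needling with cold spray to protocolized treatment.
3. State that VAS pain and location of pain are rated by unblinded patients, and report results on them in those terms.

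No arm, sample size, outcome or analysis changes. The cost is a less favourable design label and a narrower claim.

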**Discussion:**

This study aims to provide a new vision of shoulder pain, from the perspective of MPS. This syndrome can, by itself, account for shoulder pain and dysfunction, although it can coexist with real conditions involving the tendons.

**Trail Registration:**

ISRCTN Number: 30907460

## Background

Shoulder pain is an important cause of morbidity and has a high prevalence. It is the third most common musculoskeletal problem [1] seen in primary care consultations. Alteration of the soft or periarticular tissue is the most common cause [2-4], while bone disease, joint impairment (inflammatory or not) and joint instability [3,4] occurring to a lesser degree.

The origin of soft tissue lesions is quite varied. It can include a series of causes from subacromial or subacromiodeltoid bursitis to partial or total tearing of the rotator cuff tendon, calcific tendonitis of the rotator cuff, and tendonitis and rupture of the long biceps tendon [4-6]. Among these, the most common is found to be alterations in the rotator cuff, with SIS as the triggering physiopathological mechanism [7,8]. This is a problem regularly attended to in primary care [1,9].

Diagnosis is traditionally based on detailed history and clinical examination findings [1,4,10]. There are no conclusive tests included in the physical examination [3,11,12], the general practitioner's basic diagnostic tool, that allows obtaining an accurate diagnosis of alterations to the rotator cuf. A number of studies suggest that a diagnostic imaging test should be associated with the physical exploration [13,14]. US is a non-invasive method with a diagnostic precision [15] comparable to that of MRI for both, subacromial bursitis [13] and the different degrees of rotator cuff alteration [14,16]. Given the lack of clarity in clinical diagnosis, the existence of lesions in asymptomatic shoulders [17,18] and the scarce effectiveness of treatments [19,20], some authors consider that there may be another structure causing pain and dysfunction [21-23].

One solid hypothesis consists of relating rotator cuff tendonitis, as the most common cause of shoulder pain [1], with myofascial pain syndrome [23-25].

Myofascial pain syndrome is associated with differentiated, linear band-like hardness of the muscle containing hyperalgesic zones called MTrPs, which cause nociceptive agents such as substance P, potassium and histamine, among many others, to be released. These agents sensitize peripheral nociceptors and nociceptive neurones in the spinal dorsal horn [26]. The MTrP can be defined as a hyperirritable nodule that elicits local and, frequently, referred pain when pressured, situated in a palpable taut band formed by skeletal muscle fibres. It can be found either in the middle part of the muscle fibres (central MTrP) or in the areas where the muscle fibres attach to the tendon (attachment MTrP) [22,26]. With regard to clinical activity, MTrPs can be active or latent. Both cause dysfunction, but only active MTrPs produce spontaneous referred pain [22].

Specific mechanical stimulation of the MTrP, either by snapping palpation of by needling, can elicit a transient and isolated contraction of the fibres of the taut band called local twitch response (LTR) [27]. Despite its specificity, for a number of reasons, such us its low interrater reliability or the difficulties to elicit it in deep muscles, LTR is not considered an essential criterion for diagnosing MTrPs, but just a confirmatory observation [27].

According to Simon's integrated hypothesis [23,28], excessive release of acetylcholine in some dysfunctional motor endplates causes a contracture responsible for the appearance of the taut band in the affected muscle. The capillaries compression caused by the sarcomere shortening reduces local blood circulation, producing ischemia. The availability of oxygen and adenosine triphosphate (ATP) decreases, causing a local energy crisis. The resulting tissue suffering induces the release of sensitizing, substances that activate nociceptors cause pain and contribute to maintaining and further aggravating the dysfunction of the motor endplate [28]. All this would explain the palpatory findings and the increase of local pain sensitivity, that are commonly used as diagnostic criteria for MTrPs [23,29].

The dysfunction produced by trigger points is characterized by muscle shortening, muscle weakness local or referred inhibition, difficulty in relaxation, lack of coordination, fatigability and delayed recovery, spontaneous pain, pain on vigorous stretching and contracting [30]. Diagnosis of MTrPs is based on physical examination. There are no routine laboratory or imaging tests that objectively substantiate their existence [23], although in recent years specific needle electromyographic examination has become a way to objectively identify MTrPs [31-33]. Even more recently, magnetic resonance elastography [34] or Doppler US associated with US elastography [35] have shown potential to visualize the taut band or the MTrP.

There are currently different treatments for MTrPs [22,36]. The use of the mechanical stimulus of a needle to inactivate and/or eliminate the MTrP is increasing among physical therapists and other health practitioners [28,37] Since no substance is injected, the technique is commonly referred to as dry needling, and it has proven to be as effective as injection in the treatment of MTrPs by mechanically disrupting the MTrP and by activating pain control mechanisms at the spinal dorsal horn level [38].

We can see that diagnosis for SIS, rotator cuff tendonitis and MTrPs are all based mainly on medical history and physical examination [4,10,28].

Some provocation tests to provide evidence of tendonitis are not specific, since they consist of inducing a selective contraction of the muscle being tested and waiting for the pain response [10], which might also give positive results in case that muscle harboured a central MTrP, for pain (either local or referred) on contraction is also a common clinical feature of MTrPs [22,30].

In fact, we can find MTrPs that are prior to tendonitis [39,40]; they can coexist with all degenerative tendinopathy situations.

In short, we are faced with a pathological entity where suffering and degeneration are observed in the group of rotator cuff tendons caused by the impingement phenomenon, in which physiological movement is lost from lowering the humeral head [8] and the correct movement of the scapula [22]. By considering neuromuscular control as a key part of active movement, we are attempting to justify how a number of muscles affected by MTrPs can alter quality of movement, even before tendonitis occurs. MTrPs can coexist with all degenerative subacromial conditions, and perpetuate and aggravate the problem. They hinder diagnosis and render the given treatments ineffective.

### AIMS

The aims and design of the study cover two aspects: diagnosis and treatment of SIS and rotator cuff tendonitis.

### AIMS Regarding Diagnosis

- Identification of any correlation between the existence of active MTrPs and SIS and rotator cuff tendonitis.

- Identification of any correlation between the results of provocation tests for SIS and the existence of active MTrPs.

- Evaluation of the diagnostic reliability of provocation tests for SIS, using MRI and US as standard tests.

- Evaluation of the diagnostic reliability of physical exploration for active MTrPs, using US as a standard evidence.

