### In Relation to Diagnosis

Design: Transversal descriptive study

Study subjects: Patients belonging to 5 health centres in the city of Zaragoza (Spain) over the age of 18 who are diagnosed with rotator cuff tendonitis and/or SIS by a general practitioner (GP) and who give their consent after being informed about participation in the study. The minimum number of patients to be recruited is 132.

Inclusion criteria:

- Diagnosis of rotator cuff tendonitis and/or SIS by GP.

- Functional limitation and pain above 50% of the range of movement in flexion, abduction, and elevation in the scapular plane.

Exclusion criteria:

- Previous surgery for SIS

- Great limitation, pain or sudden loss of strength after suffering a traumatism that suggests another serious condition.

- Other red flag signs indicating systemic disease.

- Inability to attend intervention sessions or refusal to participate.

Study variables related to diagnosis are shown on the table 1:

**Table 1 T1:** Study Variables Related to Diagnosis

General variables	Age
	Sex
	Occupation
Pain history	Period of evolution
	Background

Previous treatments	Drug type
	Period administered
	Evolution with medication

Elevation in the scapular plane	Score on Visual Analogical Scale (VAS) Location of pain

Joint restriction (digital inclinometer)	Flexion-extension movements
	Abduction-adduction movements
	Lateral-medial rotation movements

Constant Test	

Provocation tests	Neer manoeuvre
	Jobe's test
	Hawkins test
	Yocum test
	Patte's test
	Gerber test
	Drop arm test. Painful arc test

MTrP existence by means of:	Physical examination
	Ultrasonography

The following confusion variables will be controlled: osteophytes on the lower face of the acromion, existence of latent trigger points on serratus anterior, biceps braquialis and both pectoralis, sports activity and occupation involving lifting of upper limbs above 90° of flexion or abduction.

Data analysis: a descriptive analysis will be made of the defined variables followed by a bivariate analysis by means of Pearson's r, Spearman's rho or Kendall's tau-b correlations. Multivariate analysis will be performed using logistic regression, including the variables that had a significant result in the bivariate analysis. A correlation will be established between diagnosis of SIS and rotator cuff tendonitis, positive provocation tests, existence of active MTrPs and the diagnostic results obtained with US.

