## Discussion

This study aims to provide a new vision of shoulder pain, from the perspective of MPS, a syndrome that can account for shoulder pain and dysfunction by itself, but which is perfectly compatible with the coexistence of real conditions affecting the tendons.

As previously mentioned, shoulder pain is an important cause of morbidity with a high prevalence, and a diverse and confusing background from a diagnostic perspective. GPs lack sufficient tools for its diagnosis, since it is based on a clinical examination, without conclusive tests and with few complementary tests, and its treatment (low effectiveness of the treatments described in the literature). This study aims to confirm the information obtained from the very limited literature found on the specificity and sensitivity of the provocation tests the examinater has available. Complex diagnosis complicates treatment, which is fundamental if chronicity and surgery want to be avoided.

Confirmation of the existence of active MTrPs in shoulder pain by means of their visualization with a simple diagnostic technique would allow diagnosis and, consequently, treatment to be improved.

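### The two diagnostic-accuracy aims have no matching analysis: the stated methods are correlations and a screened logistic regression, and the imaging standard for the provocation tests differs between sections

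*Protocol article*

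**What the plan says.** The protocol article lists four diagnostic aims under AIMS Regarding Diagnosis. The first two ask for correlations. The other two ask for reliability against imaging:

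- provocation tests: "Evaluation of the diagnostic reliability of provocation tests for SIS, using MRI and US as standard tests"
- MTrP examination: "Evaluation of the diagnostic reliability of physical exploration for active MTrPs, using US as a standard evidence"

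The Discussion says the study is meant to confirm the limited literature "on the specificity and sensitivity of the provocation tests".

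The data analysis under In Relation to Diagnosis plans a descriptive analysis, then a "bivariate analysis by means of Pearson's r, Spearman's rho or Kendall's tau-b correlations", then a logistic regression on the variables that were significant in that step. It closes by relating the diagnosis and the provocation tests to the "existence of active MTrPs and the diagnostic results obtained with US".

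The abstract's Method/design names both modalities: "the results obtained with ultrasonography (US) and Magnetic Renonance Imaging (MRI". Table 1 contains no MRI variable. Ultrasonography appears there only under "MTrP existence by means of".

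The Background says of MTrPs: "There are no routine laboratory or imaging tests that objectively substantiate their existence". It adds that newer elastography techniques have shown potential to make the point or its taut band visible. It also says that both active and latent points cause dysfunction, and that only active ones give spontaneous referred pain.

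**The concern.** Two of the four diagnostic aims are accuracy questions. For each test they need the proportion of imaging-positive patients who test positive and the proportion of imaging-negative patients who test negative. A correlation between two yes/no results merges these proportions with the prevalence, so it cannot tell a GP whether a test helps to rule the condition in or out. That is the gap the Discussion describes.

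The standard for the provocation tests is also unsettled. MRI and US together, or US alone, can classify the same shoulder differently, and nothing says how a discordant pair counts. If the choice is made after results are seen, the accuracy figures could follow from it.

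For MTrP examination the standard is stable, but its validity is doubtful. Active status is defined by a symptom, which an image cannot show. If US displays a latent point that the examiner rightly calls not active, an accuracy table would count this as a false negative of the examination.

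**Working it through.** **1. Aims against methods (protocol article)**

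| Diagnostic aim | Quantity needed | Stated analysis | Match |
|---|---|---|---|
| MTrPs and SIS/tendonitis | correlation | correlation | yes |
| Provocation tests and MTrPs | correlation | correlation | yes |
| Provocation tests against imaging | sensitivity, specificity | correlation, screened logistic regression | no |
| MTrP examination against US | agreement or accuracy | correlation, screened logistic regression | no |

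As described, the logistic regression has no named outcome or reference standard, so it does not supply accuracy either.

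**2. Imaging standard by place**

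| Place | Provocation tests | MTrP examination |
|---|---|---|
| Abstract, Method/design | US and MRI results | not separated |
| AIMS Regarding Diagnosis | MRI and US | US |
| Table 1 | none listed for tendon or subacromial findings | US |
| Diagnostic data analysis | US | US |

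**3. The plan's own figure.** The sample size (In Relation to Treatment) is 120 for a correlation of 0.25, error 0.05 and power 80%, raised to 132 for 10% attrition. A two-sided test of r = 0.25 against zero by the noncentral t distribution gives 120, and 120 × 1.1 = 132. The figure reproduces, and it is a size for a correlation.

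**4. What a correlation of 0.25 says about accuracy.** For two binary results with sensitivity Se, specificity Sp and prevalence p, all three correlation coefficients reduce to

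phi = (Se + Sp − 1) × √[p(1 − p) / (q(1 − q))], where q = p·Se + (1 − p)(1 − Sp) is the proportion testing positive.

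Example with p = 0.70, Se = 0.90, Sp = 0.30: q = 0.63 + 0.21 = 0.84, so phi = 0.20 × √(0.21 / 0.1344) = 0.25.

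The documents give no imaging prevalence, so a range is assumed. Specificity that gives phi = 0.25:

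| Assumed prevalence | Se 0.50 | Se 0.70 | Se 0.90 |
|---|---|---|---|
| 30% | 0.755 | 0.573 | 0.342 |
| 50% | 0.743 | 0.547 | 0.300 |
| 70% | 0.769 | 0.565 | 0.300 |
| 90% | 0.915 | 0.695 | 0.378 |

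Conversely, one fixed test with Se 0.80 and Sp 0.60 gives phi of 0.37, 0.41, 0.39 and 0.28 at these four prevalences. The coefficient moves although the test does not.

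**5. Precision if accuracy is reported.** Assume 120 evaluable patients, Se 0.80 and Sp 0.60. The Wilson 95% half-width is

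h = z·√[x(1 − x)/n + z²/(4n²)] / (1 + z²/n), with z = 1.96, x the proportion, and n = 120p for sensitivity or 120(1 − p) for specificity.

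| Assumed prevalence | n positive | h, sensitivity | n negative | h, specificity |
|---|---|---|---|---|
| 30% | 36 | 0.128 | 84 | 0.103 |
| 50% | 60 | 0.100 | 60 | 0.120 |
| 70% | 84 | 0.085 | 36 | 0.152 |
| 90% | 108 | 0.075 | 12 | 0.242 |

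All patients enter with a GP diagnosis of the condition, so a high prevalence is possible. Specificity would then rest on few patients.

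**The case against.** Much can be said on the other side.

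- **Intent and format.** The Discussion shows that the authors want sensitivity and specificity. The text is a condensed article, and a fuller plan may hold the details. This stands against inferring that accuracy will never be estimated. It does not remove the mismatch: the article does name methods for the diagnostic part, and they do not answer two of its aims.
- **Correlation is right for half of the aims.** This stands. The diagnostic analysis as a whole is not mis-specified.
- **The standard does not change for MTrP examination.** This stands. The inconsistency concerns the provocation tests only.
- **Table 1 is not exhaustive.** Acromial osteophytes, sports activity and latent trigger points are to be controlled without rows of their own, and the project outline figure is not available here. A reader might infer that imaging for SIS will not be collected. The documents do not support that, because the analysis does use diagnostic results from US. The omission is an inconsistency to repair.
- **The Background does not flatly reject US.** Its statement concerns routine tests, and the text goes on to emerging elastography methods. Comparing examination with US is therefore a legitimate aim. What remains is that shown potential does not make a truth standard, and that active status is a symptom.
- **Little is lost.** Accuracy comes from the same 2×2 tables as the correlations, provided the imaging is collected. This stands and limits the severity.

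**Conclusion.** The point holds and should be fixed. Two of the four diagnostic aims have no stated analysis that can answer them. For the provocation tests the imaging standard also differs between the aims and abstract on one side and the analysis and Table 1 on the other. For MTrP examination, US is used consistently but is weak as a truth standard for active points.

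The missing accuracy estimates follow from the choice of method, not from the shift in standard; these are two separate faults.

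The size is shown by the stated correlation of 0.25, which at every assumed prevalence from 30% to 90% is compatible with tests of very different clinical use. Useful accuracy estimates are possible, but their precision depends on the unknown prevalence. With 120 evaluable patients and assumed sensitivity 0.80 and specificity 0.60, specificity would be known to within 0.10 at 30% prevalence but only to within 0.24 at 90%.

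A reader might also infer that the sample size is miscalculated or the trial result compromised. Neither follows: 120 and 132 reproduce for the correlation stated, and the randomised comparison does not use these analyses.

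**What to change.** 1. Keep the correlations for the first two diagnostic aims.
2. For the provocation tests, reconcile the abstract, the aims, Table 1 and the data analysis to one reference standard, built from the imaging already planned and fixed before results are seen. If it combines MRI and US, say how discordant results are classified. List it in Table 1 as a tendon or subacromial finding.
3. For each provocation test, report sensitivity and specificity with 95% confidence intervals, and state that they apply to patients already diagnosed by a GP.
4. For MTrP examination versus US, report agreement on the presence of MTrPs, which both methods record in Table 1, instead of accuracy for active MTrPs.
5. State the expected precision over a range of imaging prevalence.

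The cost is analysis wording and a table row, with no added procedure as long as both modalities are still performed as the abstract and aims say. If MRI is no longer planned, the abstract and the aim must be amended to say so.
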